### 2.6. Definition and Implantation of the Thalamic Target

Under local anesthesia, a stereotaxic frame will be fixed on the patient’s head. The target will be determined by so-called “indirect” targeting, i.e., in reference to the mean coordinates of the target in relation to the anatomical landmarks constituted by the anterior (CA) and posterior (CP) commissures identified on the MRI (T1 3D SPGR sequence after injection of Gadolinium) performed under stereotactic conditions. The coordinates of the sensory thalamus are y = 2–3 mm anterior to CP; at the bi-commissural plane (z = 0). Laterally, the x-coordinate will differ depending on the topography of the pain due to the somatotopy of the ventral posterior lateral (VPL) and medial (VPM) thalamic nuclei. An x = 12–13 mm (relative to CA-CP) will be used in cases of facial pain and x = 14–15 mm in cases of upper limb pain. The entry point will be frontal, defined to avoid the trajectory crossing cortical vessels and ventricle.

The optimal position of the electrode will be refined by intraoperative electro-physiological exploration using micro-electrode recording and test stimulation [22]. Indeed, tactile or proprioceptive stimulation in the body region where the pain is located classically induces changes in the discharge pattern of the thalamic neurons corresponding somatotopically to this region. This phenomenon will be used to localize the thalamic region corresponding to the painful area and in which the lead will be implanted. Intraoperative stimulation (as well as chronic stimulation) of the VPM-VPL induces pleasant paresthesia in the contralateral body region corresponding to the stimulated thalamic area. Intraoperative test stimulation will be used to check the absence of adverse effects related to stimulation (muscle contractions, dysarthria, hot flushes, diplopia, etc.).

Once the optimal lead implantation site is identified, an octopolar electrode (Abbott Infinity 8 contact-directional lead, Chicago, IL, USA) will be implanted. The use of a directional lead will help to avoid possible side effects by preferentially steering the electrical stimulation in the optimal direction. The lead location will be checked by intra-operative X-rays images, according to the technique routinely used in each center.

### 2.7. Definition and Implantation of the Anterior Cingulate Target

The identification of the cingulate target will be done by so-called “direct targeting”, i.e., by visualization of the target on stereotactic MRI, according to the technique and location proposed by Boccard et al. [8,15]. The target is located in the dorsal anterior cingulate, approximately 20 mm posterior to the projection of the anterior tip of the frontal horn of the lateral ventricle. The trajectory will be chosen to ensure that the top three contacts of the lead are located at the junction between grey matter (cingulate gyrus) and white matter (cingulate fasciculus) and the deepest contact in the corpus callosum. The entry point will be frontal, determined to avoid the cortical vessels. The two ACC-DBS leads will be implanted bilaterally and symmetrically, without an electro-physiological exploration phase.

### 2.8. Connections to the Generators

Between 0 and 5 days after the implantation of the electrodes, a second operation will be performed, under general anesthesia, to connect the 3 electrodes to 2 dual-channel stimulators (Infinity 5 and 7, Abbott, Chicago, IL, USA) placed in 2 subcutaneous pectoral, sub clavicular, or abdominal pockets (according to the patient’s choice). The thalamic electrode will be connected to one stimulator and the cingulate electrodes to the other stimulator so that each target can be stimulated independently with different parameters.

## 3. Defining the Stimulation Amplitudes

### 3.1. Thalamic Stimulation

During the postoperative hospitalization, thalamic stimulation will be started using the contact closest to the optimal target, with the following stimulation parameters: frequency 20–100 Hz, pulse width 150 ms, amplitude 1–4 V. These stimulation parameters will be adapted to ensure that the paresthesias induced by stimulation of the sensory thalamus are pleasant and felt in the painful region. The thalamic stimulation will be used with the optimal parameters (the most effective on pain and the best tolerated) during the whole study.

### 3.2. Cingulate Stimulation

Stimulation of the ACC does not induce any perceptible feeling. The stimulation parameters used in the present study will be based on those used by Boccard et al. [15]: 4 to 6.5 Volts, frequency 130 Hz, pulse width 450 ms. To avoid a “kindling” effect and the risk of epilepsy, the chronic stimulation will be cyclic, alternating a 5-min “On” phase and a 10-min “Off” phase. The amplitude will be increased progressively, and the stimulating contacts possibly modified, depending on the therapeutic or adverse effects observed during the period between M1 and M4. The parameters found to be the most effective and best tolerated will be used for the randomized phase.

### 3.3. Statistical Analysis

Given the preliminary nature of this study, the analysis of the data concerning the efficacy of this approach will be essentially descriptive and will concern the evolution of the scores of the pain scales and neuropsychological scales over time. The results will be expressed in the form of individual graphical curves showing the evolution of these scores. These curves will make it possible to compare this evolution before and after stimulation.

The tolerance and efficacy of the combined DBS-ACC and thalamic DBS will be evaluated by comparing the postoperative scores at M22 with the preoperative scores (“baseline”). The tolerance and efficacy of DBS-ACC will be assessed by comparing the scores of each of the randomized sequences DBS-ACC “On” and DBS-ACC “Off”. Due to the small number of subjects in this study, statistical analysis will be based on non-parametric tests.

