## 2. Methods and Design

### 2.1. Study Design

The EMOPAIN study is a bicentric prospective, feasibility, and safety study to evaluate bilateral ACC-DBS combined with unilateral thalamic DBS in patients suffering from refractory chronic unilateral pain. The study design is summarized in Figure 1. The total duration of the study will be 23 months.

All patients will be treated with DBS-thalamic, activated one day after surgery and remaining active for the duration of the study in order to provide a validated and potentially effective therapeutic solution. ACC-DBS will be activated 1 month after surgery (M1), and parameter settings will be optimized during the next 3 months (M1–M4).

In order to evaluate the efficacy and safety of ACC-DBS, the study will also include a randomized phase during which DBS-ACC will be alternatively active or inactive. The lack of sensation induced by DBS-ACC will allow its double-blind evaluation. Randomization will take place 4 months after the surgery (Figure 1). The aim of the randomized phase is to compare the combination of DBS-ACC and DBS-thalamic with DBS-thalamic alone, with the patient as his own control, in two 3-month periods organized in a cross-over design. The thalamic stimulation will be left on throughout this phase. The patient will be randomized (centralized randomization) between a DBS-ACC sequence on (“On”) and a DBS-ACC sequence off (“Off”), these parameters being set by the neurosurgeon. Patients and evaluating neurologists will be blinded for the results of randomization. The two sequences will be separated by a two-week wash-out period to avoid a residual effect. Evaluation data will be collected by the neurologist at the end of each sequence (M7 and M10).

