### 2.3. Patients

We will include 10 adult patients (age 18–70 years old) suffering from chronic (duration > 1 year) unilateral neuropathic pain, severe (VAS score > 6/10), with high emotional impact (HAD sub-scores > 10), considered resistant to medication specific to neuropathic pain at sufficient doses and durations (including at least antiepileptics and antidepressants), and not sufficiently improved by rTMS and relevant surgical solutions. Patients who respond to rTMS will not be included as they may potentially respond to cortical stimulation, a technique considered to be less invasive than DBS.

Non-inclusion criteria will be cognitive impairment (MMSE score < 24), DSMIV axis I psychiatric disorder, and contra-indication to surgery, DBS, anesthesia, or MRI.

Considering the pioneering nature of this study and the number of patients required in similar pilot studies exploring the effects of DBS in emerging indications, it seems to us that 10 patients would be sufficient to achieve the objectives of this project.

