## 4. Discussion

In this article, we describe the rationale and design of an ongoing prospective, double-blind, parallel-group multicenter RCT to evaluate the feasibility and safety of bilateral ACC-DBS combined with unilateral thalamic DBS in patients suffering from chronic unilateral pain, refractory to medical treatment.

Until now, the only available data on the possible efficacy of ACC-DBS comes from small, open studies, which are insufficient to prove effectiveness and classify ACC-DBS as a regular therapy. On another hand, thalamic DBS has been proposed for years to treat intractable pain. We aim to evaluate the efficacy of combined ACC-DBS and thalamic-DBS because preliminary data suggested that these two approaches may be complementary to improving chronic pain patients. However, the design of our study might allow obtaining a clue to the respective effects of each DBS target, as thalamic DBS will be used alone for one month, and ACC-DBS will be evaluated in a cross-over On/Off trial. The efficacy of these single and combined DBS effects will be evaluated not only using pain intensity measures (VAS, Brief Pain Inventory, McGill Pain Questionnaire) but also using emotional pain impact and quality of life assessments (SF36, EQ5D).

Before going further in its therapeutic development, it appears to be essential to evaluate the cognitive, emotional, and affective consequences of DBS-ACC.

We will include only patients suffering from chronic neuropathic pain. In a meta-analysis, Bittar et al. [5] showed that DBS of the sensory thalamus was more efficient on nociceptive pain than neuropathic pain. However, nociceptive pain may be more easily controlled by pharmacological approaches than neuropathic pain. In their study evaluating ACC-DBS in 16 patients, Boccard et al. [15] included various etiologies of chronic pain (brachial plexus injury, post-stroke pain, and spinal pathology, including traumatism and FBSS), but efficacy did not differ across etiologies. ACC-DBS is supposed to modulate the affective component of pain, whatever the cause of pain.

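### The only randomised contrast, ACC-DBS On against Off, is stated with no allowance for period; in a 10-patient cross-over this costs power if orders are balanced and adds bias if they are not

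*Protocol article*

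**What the plan says.** Section 2.1 (Study Design) sets the randomised phase "with the patient as his own control, in two 3-month periods organized in a cross-over design". A wash-out separates the periods, and outcomes are collected at the end of each, at M7 and M10. Randomisation is centralised; the ratio of On-first to Off-first patients is not given.

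Section 3.3 (Statistical Analysis) gives the randomised comparison: the tolerance and efficacy of ACC-DBS "will be assessed by comparing the scores of each of the randomized sequences", On and Off. It adds: "Due to the small number of subjects in this study, statistical analysis will be based on non-parametric tests". No test is named, and neither period nor treatment order is mentioned. Sections 2.1 and 3.3 both use the word sequence for the On or Off condition, so no term is left for the order in which a patient receives them. Section 3.3 also calls the efficacy analysis mainly descriptive, shown as individual curves.

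Section 2.3 (Patients) sets the size by precedent: "it seems to us that 10 patients would be sufficient to achieve the objectives of this project". No effect size, SD, significance level or power is stated.

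The Discussion opens by calling the study "an ongoing prospective, double-blind, parallel-group multicenter RCT", yet its next paragraph says that "ACC-DBS will be evaluated in a cross-over On/Off trial".

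**The concern.** In a two-period cross-over, anything that changes between M7 and M10 irrespective of ACC stimulation enters every patient's On-Off difference. It enters with one sign in patients who had On first and the opposite sign in those who had Off first. A plain paired comparison does not separate this from the treatment effect.

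The article itself gives reasons to expect such a change. Randomisation comes four months after surgery and straight after the setting of the ACC parameters. The assessments are scheduled before surgery and at M1, M4, M7 and M10, so practice on the cognitive tests could continue into the second period. That bears directly on the tolerance comparison.

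This contrast is the trial's only randomised evidence on ACC-DBS, for both efficacy and tolerance, and it rests on 10 patients. A period effect could hide a real difference or, with unequal orders, shift the estimate.

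**Working it through.** **Inputs.** From the article: 10 patients, two periods, On and Off within patient, non-parametric testing. There is no power calculation to reproduce. Assumed, because the article gives no values: SD of the within-patient On-Off difference 1.5 VAS points, true effect 1.5 points (1 SD), normal errors, no carry-over, two-sided 5% level. The period effect is varied from 0 to 3 points and the split of orders from 5:5 to 8:2.

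**Bias of the plain mean.** Let the effect be t and the period effect p, both scored as improvement, with p favouring the second period. The expected On-Off difference is t − p in On-first patients and t + p in Off-first patients. The plain mean over 10 patients is therefore

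t + p × (n_OffFirst − n_OnFirst)/10.

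- 5:5: bias 0.
- 6:4: 0.2p in size.
- 7:3: 0.4p. With p = 1 and t = 1.5, the mean is 1.1 (seven On-first) or 1.9 (seven Off-first).
- 8:2: 0.6p.

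If randomisation were unrestricted, which the article does not say, the probability of exactly 5:5 would be 252/1024 = 0.25, and of 7:3 or worse 352/1024 = 0.34.

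**Period-adjusted estimate.** Take the first-period minus the second-period result for each patient, on the same scale. Its expectation is t − p in On-first patients and −t − p in Off-first patients. The group difference is 2t, so half of it is t whatever p is. A common shift p does not change the comparison between groups, so the power of any test of that comparison is independent of p.

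**Power at 5:5 (simulation).**

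| Period effect (points) | Signed-rank on On-Off | Exact permutation of period differences | Exact rank-sum of period differences |
|---|---|---|---|
| 0 | 0.79 | about 0.78 | 0.68 |
| 0.75 | 0.70 | about 0.78 | 0.68 |
| 1 | 0.63 | about 0.78 | 0.68 |
| 1.5 | 0.44 | about 0.78 | 0.68 |
| 3 | 0.02 | about 0.78 | 0.68 |

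A larger effect of 1.25 SD (1.25 × 1.5 = 1.875 points) gives the same pattern. Signed-rank power is 0.93, 0.88 and 0.68 at period effects of 0, 0.75 and 1.5 points, against 0.86 throughout for the rank-sum test.

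**Unequal orders.** At 7:3 with seven On-first and a 1-point period effect, signed-rank power is 0.38 and permutation power 0.71. With no period effect at 7:3, the figures are 0.78 and 0.71.

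**Type I error of the signed-rank test.** At 5:5 it is 0.048, 0.029, 0.006 and 0.000 for period effects of 0, 0.5, 1 and 2 SD, so the test is conservative. At 7:3 it stays at about 0.04 to 0.06. Only at 8:2 is it clearly inflated, at 0.10 to 0.26 for period effects of 0.5 to 2 SD.

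**The case against.** The strongest reply is that section 3.3 names a contrast, not a test. A rank or permutation test of period differences is itself non-parametric and would satisfy "statistical analysis will be based on non-parametric tests". A condensed article may leave that choice to the full protocol or analysis plan, which are not shown. This stands to the extent that a reader who infers that the trial has settled on a period-blind test goes further than the text. What remains is that the contrast as worded gives period and order no role, and that the wording uses up the term needed for order.

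A reader might also infer that any time trend biases the result or destroys its power. The documents do not support that. At 5:5 the mean is unbiased and the test errs on the safe side. A trend of 0.75 point leaves the plain test at 0.70, slightly above the adjusted rank-sum test at 0.68. The article does not state the ratio of orders, so imbalance is a possibility and not a fact.

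The efficacy analysis is declared mainly descriptive and no power is promised, so a loss of power breaches no stated property. This lowers the severity. It does not remove the point: tests are announced, and bias under unequal orders would affect a descriptive On-Off mean just as much.

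Finally, parallel-group might be read as announcing an independent-groups analysis. The abstract, section 2.1, the legend of Figure 1 and the Discussion itself all say cross-over, so it is a one-word slip.

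**Conclusion.** The point holds in a limited form. The stated randomised contrast makes no allowance for period in a design where a period or practice trend is plausible. If it is carried out as a plain paired comparison, there are two consequences. With unequal orders the mean is biased, by 0.4 of the period effect at 7:3. With 5:5 orders there is no bias, but power falls from 0.79 to 0.63 at a period effect of 1 point and to 0.44 at 1.5 points, while a period-adjusted permutation test keeps about 0.78. Small trends cost little.

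The power figures rest on the assumed SD and effect of 1.5 points, normal errors and no carry-over; the bias formula needs only the absence of carry-over. The size of any real period effect is unknown. Severity: should be fixed. The design label in the Discussion is an editorial correction.

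**What to change.** - In section 3.3, state that first-minus-second-period differences will be compared between the On-first and Off-first groups by an exact permutation test.
- Report half the group difference, with its exact 95% confidence interval, as the period-adjusted On-Off effect, and show results by order.
- Allocate the two orders 5:5 if that is still open, and state the ratio.
- Call On and Off conditions or periods, and keep sequence for treatment order.
- In the Discussion, replace parallel-group by cross-over.

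Cost: wording only, with no new data or visits. Under the assumptions above, when there is no period effect the permutation test gives up about 1 point of power at 5:5 (about 0.78 against 0.79) and about 7 points at 7:3 (0.71 against 0.78), which is a further reason to balance the orders. The rank-sum version is less attractive because its discreteness costs about 11 points at 5:5 (0.68 against 0.79).

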## 4. Discussion

In this article, we describe the rationale and design of an ongoing prospective, double-blind, parallel-group multicenter RCT to evaluate the feasibility and safety of bilateral ACC-DBS combined with unilateral thalamic DBS in patients suffering from chronic unilateral pain, refractory to medical treatment.

Until now, the only available data on the possible efficacy of ACC-DBS comes from small, open studies, which are insufficient to prove effectiveness and classify ACC-DBS as a regular therapy. On another hand, thalamic DBS has been proposed for years to treat intractable pain. We aim to evaluate the efficacy of combined ACC-DBS and thalamic-DBS because preliminary data suggested that these two approaches may be complementary to improving chronic pain patients. However, the design of our study might allow obtaining a clue to the respective effects of each DBS target, as thalamic DBS will be used alone for one month, and ACC-DBS will be evaluated in a cross-over On/Off trial. The efficacy of these single and combined DBS effects will be evaluated not only using pain intensity measures (VAS, Brief Pain Inventory, McGill Pain Questionnaire) but also using emotional pain impact and quality of life assessments (SF36, EQ5D).

Before going further in its therapeutic development, it appears to be essential to evaluate the cognitive, emotional, and affective consequences of DBS-ACC.

We will include only patients suffering from chronic neuropathic pain. In a meta-analysis, Bittar et al. [5] showed that DBS of the sensory thalamus was more efficient on nociceptive pain than neuropathic pain. However, nociceptive pain may be more easily controlled by pharmacological approaches than neuropathic pain. In their study evaluating ACC-DBS in 16 patients, Boccard et al. [15] included various etiologies of chronic pain (brachial plexus injury, post-stroke pain, and spinal pathology, including traumatism and FBSS), but efficacy did not differ across etiologies. ACC-DBS is supposed to modulate the affective component of pain, whatever the cause of pain.

However, it is possible that certain pain etiologies may respond better to ACC-DBS than others. In our study, the pathophysiology of pain will be relatively homogenous; only patients with chronic refractory neuropathic pain will be included. We will not include patients with post-stroke pain in this study to ensure the structural integrity of the neural networks that potentially support the DBS-ACC mechanism(s) of action.

We expect DBS-ACC to be successful in chronic and refractory neuropathic pain and to be well tolerated. We expect that its effect on the emotional and affective components of pain will not be accompanied by undesirable consequences on the overall cognitive, affective, and emotional functioning of patients. This would confirm the interest in DBS-ACC as a potential alternative or complement to DBS-thalamic and would offer refractory chronic pain patients a new therapeutic option.

This study will also allow the collecting of data for the construction of a larger study.

## Figures and Tables

**Figure 1 brainsci-12-01116-f001:**
[figure not shown]
Study design. The study design consists of a 1-month pre-treatment evaluation phase, a phase of thalamic stimulation alone (1 month), and then thalamic and cingulate stimulation (3 months M1 to M4). A 6.5-month cross-over randomized phase will compare DBS-ACC combined with thalamic DBS to thalamic DBS alone (M4 to M7 and M7 to M10). Then a 12-month open phase will evaluate the long-term effect of combined DBS-ACC and thalamic DBS stimulation (M10 to M22).

## Data Availability

Not applicable.
